## Abstract

**Background:** Non-adherence to direct oral anticoagulants (DOACs) remains a matter of concern, especially for patients with a recent stroke. However, data on electronically monitored adherence and adherence-improving interventions are scarce.

**Aims:** We aim to use electronic monitoring in DOAC-treated stroke patients to (i) evaluate the effect of an educational, reminder-based adherence-improving intervention, (ii) investigate predictors of non-adherence, (iii) identify reliable self-report measures of adherence, and (iv) explore the association of non-adherence with clinical outcomes.

**Methods:** Single-center, randomized, crossover, open-label study. Adherence to DOACs of polymedicated patients self-administering their medication will be monitored electronically throughout the 12-month-long study following hospitalization for ischemic stroke. After a 6-month observational phase, patients will receive pharmaceutical counseling with feedback on their intake history and be given a multi-compartment pillbox for the subsequent 6-month interventional phase. The pillbox will provide intake reminders either during the first or the last three interventional-phase months. Patients will be randomly allocated to reminders-first or reminders-last.

**Study outcomes:** Primary: non-optimal timing adherence; Secondary: non-optimal taking adherence; timing adherence; taking adherence; self-reported adherence; clinical outcomes including ischemic and hemorrhagic events; patient-reported device usability and satisfaction.

**Sample size estimates:** A sample of 130 patients provides 90% power to show a 20% improvement of the primary adherence outcome with intake reminders.

**Discussion:** MAAESTRO will investigate various aspects of non-adherence and evaluate the effect of an adherence-improving intervention in DOAC-treated patients with a recent stroke using electronic monitoring.

**Clinical Trial Registration:** ClinicalTrials.gov identifier: NCT03344146, Swiss National Clinical Trials Portal SNCTP000002410

## Background and aims

Non-adherence to direct oral anticoagulants (DOACs) remains a matter of concern due to their short half-lives and lack of coagulation monitoring (1). So far, research on adherence to DOACs has been sparse and inconsistent, especially among patients treated for recurrent stroke prevention. Studies using self-reporting (2, 3) and prescription claims data (1) yielded discrepant results on the extent of non-adherence and failed to identify concrete predictors. Although electronic monitoring is considered the most accurate method in adherence research (4), data remain scarce (5).

Non-adherence to DOACs is associated with increased risk for stroke, bleeding, and death (1, 2). The need for effective adherence-improving strategies is increasingly recognized (5, 6). Patients with a recent stroke are at high risk for both recurrence and non-adherence due to neurological and cognitive deficits (7). Although they would especially benefit from adherence-improving interventions, to our knowledge just one study used electronic devices to enhance adherence in DOAC-treated stroke patients (8). So far, no studies investigated multi-compartment compliance aids (MCCAs) with reminder function, i.e., compartmentalized pillboxes with discrete sections for each dosing occasion that also provide audiovisual intake reminders.

We aim to use electronic monitoring and reminder-delivering MCCAs in DOAC-treated patients with a recent stroke to evaluate the effect of an educational, reminder-based adherence-improving intervention, investigate predictors of non-adherence, identify reliable self-report measures of adherence, and explore the association of non-adherence with clinical outcomes. Our main hypothesis is that intake reminders improve adherence.

## Methods

### Design

This is a single-center, randomized, crossover, open-label study. Figure 1 shows the study flowchart and Table 1 the assessments schedule.

**Figure 1 F1:**
[figure not shown]
Study flowchart.

**Table 1 T1:** Assessments schedule.

		**Visit 0**	**Visit 1**	**Visit 2**
Baseline characteristics (demographics, medical history, stroke details including neuroimaging etc.)^*^		✔		
Modified Rankin Scale (mRS)^*^		✔	✔	
National institutes of Health Stroke Scale (NIHSS)		✔		
Montreal Cognitive Assessment (MoCA) (9)		✔		
Adherence electronic monitoring				
Intercurrent medical history (clinical events, DOAC treatment interruptions etc.)^*^				
Structured interview with counseling, including:			✔	✔
Questionnaires	Polymedication-Check		✔	✔
	Adherence self-report (10) (modified for DOACs)		✔	✔
	A-14 scale (11)		✔	✔
	Patient-reported preference and satisfaction with DOACs		✔	✔
	Patient-reported device usability and satisfaction (12) (modified)			✔

* *Information will be compiled from the electronic hospital record, external sources (e.g., general practitioner, pharmacy) and patient anamnesis as appropriate. The mRS will be assessed during the clinical visit interview. Clinical events as diagnosed by the patients' treating physicians will be recorded*.

### Patient Population

Inclusion criteria:

Age ≥ 18 yearsHospitalization for ischemic strokeDOAC (dabigatran, rivaroxaban, apixaban, edoxaban) treatment for recurrent stroke prevention (e.g., in non-valvular atrial fibrillation or other indications)Polypharmacy (≥ 3 medications, including DOACs)Medication self-administration

Exclusion criteria:

Medication administration by a third person (pillbox prefilling by a third person, physical disability and cognitive deficits do not exclude patients provided they self-administer their medication)Unable or unwilling to participate

### Randomization

Patients will be openly randomized to one of two groups in a 1:1 ratio at visit 1 in a crossover design: During the 6-month interventional phase, Group 1 will receive intake reminders for the first 3 months and Group 2 for the last 3 months. Randomization will be performed by a central computer through the web-based electronic case report form and include a variance minimization algorithm to ensure balancing for sex, age, NIHSS, and prior pillbox use.

### Intervention

Key methodological instrument for MAAESTRO is the novel *Time4Med* medication system (Adherence Innovations, Hong Kong, China) which includes (i) the *Smart Card*, a small electronic device featuring a button that records intake date and time when pressed, (ii) the *Reminder Card*, a small electronic device that provides audiovisual intake reminders, and (iii) a MCCA with discrete medication storage compartments for each time of the day and day of the week, upon which the Reminder Card can be attached. Patients will record their intakes using Smart Cards throughout the 12-month-long study. After the 6-month observational phase, patients will receive pharmaceutical counseling during a medication review, the Polymedication-Check (13), and feedback on their intake history (Visit 1). Based on these, the optimal intake timepoints will be identified for each patient. Patients will receive MCCAs for use throughout the 6-month interventional phase along with attachable Reminder Cards, which will be programmed to provide reminders at the optimal timepoints for either the first or the last 3 months.

### Study Outcomes

The primary outcome is non-optimal timing adherence to DOACs, defined as ≥ 1 dose omitted or taken outside of 25% of the prescribed dosing schedule (± 6 h for once-daily and ± 3 h for twice-daily DOACs). It will be calculated for the observational phase and for the two interventional-phase periods separately. Physician-initiated temporary treatment interruptions will not be considered non-adherence.

Secondary outcomes are:

non-optimal taking adherence (i.e., ≥ 1 dose omitted)timing adherence (i.e., proportion of doses taken within 25% of the prescribed dosing schedule)taking adherence (i.e., proportion of prescribed doses taken)self-reported adherence (based on the “Adherence self-report” and “A-14 scale” questionnaires, Table 1)clinical events including recurrent ischemic stroke, other ischemic events, bleeding and deathpatient-reported device usability and satisfaction

### Sample Size Estimates

A sample of 130 participants is required to show a significant difference in non-optimal timing adherence with reminders, based on simulations using a mixed-effects logistic model with a power of 0.9 and a two-sided 0.05 alpha level and assuming (i) 20% adherence-enhancing effect of reminders, (ii) 45% rate of non-optimal timing adherence without reminders and (iii) 12% drop-out rate. These assumptions were informed by our previous experience with this patient population (3).

### Statistical Analyses

The primary analysis will evaluate the reminders' effect on the primary outcome with a mixed-effects logistic model with Reminder Card (yes/no) as fixed and patient as random effect. Ancillary analyses will include the addition to the model of the following covariates:

the interventional-phase period (first/second), in order to assess for period effects (adherence differences between the two periods independent of the reminders' effect). We designed the study with a crossover design, assuming that adherence will be generally stable over the relatively short study duration and thus no period effects are expected.the interaction term “Reminder Card ^*^ period”, in order to assess for modification of the reminders' effect by the interventional-phase period (e.g., through a “carry-over effect”). We expect any interaction to be negligible.the type of DOAC (once-/twice-daily), in order to assess for association between adherence and type of DOAC.the interaction term “Reminder Card ^*^ type of DOAC”, in order to assess for modification of the reminders' effect by the type of DOAC.

Secondary analyses include the comparison of adherence outcomes between (i) the two interventional-phase periods and (ii) observational and interventional phase, as in the primary analysis. Non-adherence predictors (e.g., clinical and neuroimaging variables, mRS, MoCA test scores) will be assessed using logistic mixed lasso models. Descriptive statistics will be used for the comparison of self-reported with electronically recorded adherence, the association between adherence and clinical events and to present the rest of the data.

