## Discussion

MAAESTRO is designed with pragmatic eligibility criteria to ensure participants are as representative as possible of stroke survivors self-administering their medication. Our study uses MCCAs and includes polymedicated patients, for whom pillbox use is meaningful, as they comprise the vast majority of stroke patients in clinical practice (3).

To obtain objective adherence data in a real-life setting, we use electronic monitoring during a long observational phase without further interventions that might modify medication-taking behavior (4). This will allow us to search for non-adherence predictors, with emphasis on cognitive and neuroimaging characteristics, and for reliable self-report measures of adherence that best discriminate adherers from non-adherers. These will provide healthcare professionals with simple, inexpensive ways to identify patients at risk for non-adherence.

For the adherence-improving intervention we hypothesize that reminders will have the largest effect (14). We therefore designed and powered MAAESTRO to provide randomized evidence for their use. We expect that counseling and MCCAs will have an additional adherence-improving effect, which we will assess in before-after comparisons. Furthermore, we will capture patient-reported device usability and satisfaction to complement the intervention's evaluation.

MAAESTRO is not powered to determine the impact of non-adherence on clinical outcomes. However, the detailed electronic intake records will allow close examination of possible deviations preceding clinical outcomes on an individual basis, which may provide insights into the mechanisms of stroke and bleeding occurrence in DOAC-treated patients.

In summary, MAAESTRO will provide comprehensive data on electronically monitored adherence and most importantly, randomized evidence for an adherence-improving intervention in the yet unexplored population of DOAC-treated patients with a recent stroke. Patient enrolment began in January 2018.

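### The primary crossover model leaves out period on an unsupported assumption of stable adherence; promoting the period-adjusted model already planned would be a small improvement at essentially no cost

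*Protocol article*

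**What the plan says.** The Statistical Analyses section of the protocol article specifies the primary analysis as a logistic mixed model "with Reminder Card (yes/no) as fixed and patient as random effect". Among the covariates reserved for ancillary analyses is "the interventional-phase period (first/second), in order to assess for period effects". The reason given is that the crossover was designed "assuming that adherence will be generally stable over the relatively short study duration and thus no period effects are expected". A Reminder Card by period interaction is also planned as ancillary, and a comparison of the two interventional periods is listed as a secondary analysis.

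The Intervention section sets the timing: "After the 6-month observational phase, patients will receive pharmaceutical counseling during a medication review", together with feedback on the recorded intakes, at Visit 1. It adds: "Patients will receive MCCAs for use throughout the 6-month interventional phase". The Discussion states "We expect that counseling and MCCAs will have an additional adherence-improving effect", to be assessed by comparing before with after.

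**The concern.** Period is a structural factor of a two-period crossover, and the usual model includes it whether or not a period effect is expected. Here the primary model excludes it because adherence is assumed stable, and the article gives no data for that.

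The assumption is open to doubt. Counseling and feedback are scheduled at Visit 1, just before the first reminder period. The first period therefore covers months 0-3 after them and the second covers months 3-6. If their effect fades, or if pillbox habits take time to form, the two periods differ regardless of reminders.

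Two things are at stake. In a logistic mixed model, leaving out a real fixed effect pulls the reminder odds ratio towards 1 even when the sequences are balanced. If the sequences are unequal at analysis, part of the period effect is also counted as a reminder effect.

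**Working it through.** **Inputs from the article (Sample Size Estimates, Randomization).** 130 patients, power 0.90, two-sided alpha 0.05, 45% non-optimal timing adherence without reminders, a 20% effect, 12% drop-out, 1:1 allocation to two sequences. Completers: 130 × 0.88 = 114.4, about 114.

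**Assumptions, because the article gives no value.** The 20% is read as absolute (45% to 25%). The random-intercept SD is 1 or 2. The period odds ratio is 1, 1.5, 2 or 3.

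**Step 1: reproduce the 130.** For paired binary outcomes, with discordance p_d, difference d = 0.20 and within-patient correlation ρ:

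n = [1.96·√p_d + 1.2816·√(p_d − d²)]² / d², where p_d = 0.45·0.75 + 0.55·0.25 − 2ρ·√(0.45·0.55·0.25·0.75).

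- ρ = 0: p_d = 0.475, n = 121 completers, 138 after dividing by 0.88.
- ρ = 0.05: p_d = 0.453, n = 115, or 131 with drop-out.
- ρ = 0.10: p_d = 0.432, n = 110, or 125 with drop-out.

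So 130 is reproduced at a weak correlation of about 0.05. A relative 20% (45% to 36%) does not reproduce it: power at 114 completers is 0.28-0.49 for ρ from 0 to 0.5. The absolute reading is used below.

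**Step 2: the model.** For patient i in period j,

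logit P(non-optimal) = α + τ·reminder + π·(j − 1.5) + u_i, with u_i ~ N(0, σ²).

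α and τ are set so that the population rates are 45% and 25%. This gives τ = −1.072 for σ = 1 and −1.452 for σ = 2. Both models were fitted to expected cell counts, and power was taken from the likelihood-ratio noncentrality.

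**Step 3: balanced sequences (57/57).** The model with period returns the true τ in every row.

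| σ | Period OR | log OR without period | Shrinkage | Power without | Power with |
|---|---|---|---|---|---|
| 1 | 1 | −1.072 | 0% | 0.927 | 0.927 |
| 1 | 1.5 | −1.055 | 1.6% | 0.923 | 0.926 |
| 1 | 2 | −1.022 | 4.7% | 0.913 | 0.923 |
| 1 | 3 | −0.955 | 10.9% | 0.889 | 0.917 |
| 2 | 1 | −1.452 | 0% | 0.974 | 0.974 |
| 2 | 1.5 | −1.430 | 1.5% | 0.972 | 0.973 |
| 2 | 2 | −1.391 | 4.2% | 0.969 | 0.972 |
| 2 | 3 | −1.310 | 9.8% | 0.959 | 0.970 |

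Shrinkage is (|true| − |estimate|)/|true|; for example (1.072 − 0.955)/1.072 = 10.9%.

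**Step 4: no true reminder effect.** The reminder-on minus reminder-off contrast has expectation τ − π in the reminders-first group and τ + π in the reminders-last group. Pooled without period, it is roughly τ + π·(n₂ − n₁)/(n₁ + n₂).

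- 57/57: the period term cancels. Bias is 0 and type I error is about 0.05 even at a period odds ratio of 3.
- 62/52: roughly −(10/114)·π = −0.088·π. With π = ln 1.5, ln 2 and ln 3 (0.405, 0.693, 1.099) this gives −0.036, −0.061 and −0.096. The fitted logistic model gives −0.035, −0.058 and −0.088, with type I error at most about 0.06. Reversing the imbalance reverses the sign.
- 65/65 with 6% versus 18% lost after the first period: bias at most 0.046 in size, type I error at most 0.052.

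**Step 5: unequal loss with a real reminder effect.** If the bias from unequal loss runs towards zero, it adds to the shrinkage. With 18% versus 6% loss, σ = 1 and a period odds ratio of 3, power is 0.885 without period and 0.930 with it, a loss of 4.5 points. The range of 0-3 points therefore applies to balanced sequences.

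**The case against.** A reader might infer that the article contradicts itself by expecting counseling and pillbox to change adherence while expecting no period effect. The text does not support that. The Discussion's expected gain is a contrast between the observational and interventional phases, whereas the stability assumption concerns the first against the second interventional period. Both groups are counseled before the first period and keep the pillbox through both. A step at Visit 1 is not a difference between the periods. That needs fading or build-up, which the article nowhere states. This part of the objection stands.

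It is also true that period is not ignored. The adjusted model, the interaction and a direct comparison of periods are all prespecified, and one model is clearly named as primary. The question is only which planned model carries that label.

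The larger period effects are demanding as well. A reminder log odds ratio of −1.072 corresponds to an odds ratio of about 2.9 in the other direction (exp 1.072 = 2.92). A period odds ratio of 3 would therefore match the whole reminder effect at σ = 1, although the Discussion hypothesizes that reminders have the largest effect. At 1.5 the loss is barely visible.

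Finally, attenuation is conservative, and 1:1 allocation with minimization makes gross imbalance unlikely at randomization. A 62/52 split from 65/65 would need 3 versus 13 losses, or 4.6% versus 20%. What remains is that the assumption is unsupported and dropping it costs essentially nothing.

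**Conclusion.** The point holds as an optional improvement. The primary model rests on an unsupported assumption of stability between the two interventional periods. If the assumption fails, balanced sequences give an estimate shrunk by about 1-2%, 4-5% or 10-11% at period odds ratios of 1.5, 2 or 3, with about 0-3 points of power lost. At an odds ratio of 2, power without period is still 0.913 or higher. Only at 3 with σ = 1 does it fall just below the planned 0.90, to 0.889.

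A reader might infer that the primary test is invalid. It is not: with balanced sequences there is no null bias and no type I inflation. With a 62/52 split the null bias is 0.035-0.088 on the log scale and type I error stays at or below about 0.06.

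These sizes rest on the absolute reading of the 20% effect and on assumed random-intercept SDs, period odds ratios and imbalance patterns. The article gives none of the last three.

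**What to change.** Specify the primary model as non-optimal timing adherence on Reminder Card (yes/no) and interventional-phase period (first/second) as fixed effects, with patient as random effect. Report the model without period as ancillary, and drop the expected absence of period effects as the reason for the choice of model.

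The cost is one degree of freedom and one sentence, since the adjusted model is already planned. With no period effect, power is 0.927 either way at σ = 1 and 0.974 either way at σ = 2, so the sample size of 130 need not change. The change should be fixed before the outcome data are analyzed, so that it is settled in advance which result counts if the two models disagree near the 0.05 threshold.

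### The once- v twice-daily comparison on the any-deviation outcome shows a regimen difference even when per-dose adherence is the same

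*Protocol article*

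**What the plan says.** Under Study Outcomes in the protocol article, the primary outcome is binary, "defined as ≥ 1 dose omitted or taken outside of 25% of the prescribed dosing schedule", with windows of ± "6 h for once-daily and ± 3 h for twice-daily DOACs". One value is scored per phase or period: "It will be calculated for the observational phase and for the two interventional-phase periods separately". Each interventional period lasts 3 months (Randomization).

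Under Statistical Analyses, the primary model is a mixed-effects logistic regression of that flag on Reminder Card, with patient as random effect. Among the covariates then added as ancillary analyses are "the type of DOAC (once-/twice-daily), in order to assess for association between adherence and type of DOAC" and its interaction with Reminder Card. The model as described has no offset or other term for the number of doses.

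Two secondary outcomes do have doses in the denominator: timing adherence and taking adherence, both defined as proportions.

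**The concern.** The probability of at least one deviation rises with the number of opportunities. A twice-daily regimen has twice as many doses per period, so it produces more patients scored non-optimal even if the per-dose chance of a lapse is identical. The timing window is scaled to the dosing interval, but nothing is scaled for the number of doses. The DOAC-type coefficient therefore mixes dose count with behaviour and cannot separate them.

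At stake is the conclusion drawn from this ancillary analysis. A report that adherence is poorer on twice-daily DOACs could be a product of the outcome definition alone.

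**Working it through.** **Inputs from the article.** Rate without reminders 45% (Sample Size Estimates); 3-month periods (Randomization); outcome is at least one deviation in the period (Study Outcomes).

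**Assumptions, not in the article.** Half the patients are on each regimen; 3 months is 13 weeks, i.e. 91 once-daily or 182 twice-daily doses; doses are independent given the patient; equal behaviour means equal per-dose deviation risk. Between-patient spread is unknown, so a range is shown.

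**The plan's own figure.** I read the planned effect as 45% to 25%. The unpooled two-proportion formula gives (1.960 + 1.282)² × (0.45×0.55 + 0.25×0.75) / 0.20² = 10.507 × 0.435 / 0.04 = 114.3 patients. Dividing by 0.88 for drop-out gives 129.9, i.e. the stated 130. So 45% is a rate per 3-month period, and the planned effect is 20 percentage points.

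**Homogeneous risk.** Let x be the probability that a once-daily patient has no deviation in the period. With twice the doses, a twice-daily patient has probability x². Setting the average rate to 45%:

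1 − (x + x²)/2 = 0.45, so x² + x = 1.1 and x = (−1 + √5.4)/2 = 0.6619.

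- Once daily: 1 − 0.6619 = 33.8%
- Twice daily: 1 − 0.4381 = 56.2%
- Odds ratio: (0.5619/0.4381) / (0.3381/0.6619) = 2.51

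**Heterogeneous risk.** Let patients' deviation rates follow a gamma distribution with shape k, with mean number of deviations L once daily and 2L twice daily. Then P(at least one) = 1 − (1 + L/k)^(−k). Solving for L so that the two regimens average 45%:

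| Spread | L | Once daily | Twice daily | Odds ratio |
|---|---|---|---|---|
| None | 0.413 | 33.8% | 56.2% | 2.51 |
| k = 1 | 0.575 | 36.5% | 53.5% | 2.00 |
| k = 0.5 | 0.817 | 38.4% | 51.6% | 1.71 |
| k = 0.25 | 1.769 | 40.7% | 49.3% | 1.42 |

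The size shrinks as patients differ more, but the direction does not change. These odds ratios come from population-average rates; a random-intercept coefficient is conditional on the patient and would generally lie further from 1.

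**A different anchor.** Taking 45% as the once-daily rate over 90 doses, 180 doses give 1 − 0.55² = 69.75%, odds ratio 2.82. A normal spread in the logit of the per-dose risk with SD 1, 2 and 3 gives 2.09, 1.61 and 1.41. The range is much the same.

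**Interaction.** Suppose reminders cut the per-dose rate by the same factor in both regimens, taking the average from 45% to 25%. With homogeneous risk, x² + x = 1.5 gives x = 0.8229, so the rates become 17.7% and 32.3%. The reminder odds ratio is then 0.421 once daily and 0.372 twice daily, a ratio of 0.88 where there is no interaction per dose. The same calculation gives 1.00 at k = 1 and 1.13 at k = 0.25. This artefact is smaller than that in the main effect, and its direction depends on the heterogeneity.

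**Window.** None of these figures includes the narrower twice-daily window. If patients had equal scatter in clock hours, it would widen the gap.

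**The case against.** The case for leaving the plan alone has four parts.

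*It is only ancillary.* DOAC type is not randomised, is not the main hypothesis and did not drive the sample size. That is true and limits the severity. It does not rescue the stated purpose of the analysis, which is to assess an association with adherence.

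*The size is uncertain.* The odds ratio of 2.5 needs equal risk in every patient and an assumed regimen mix. With 57 patients per regimen in one period, the 45%-once-daily anchor gives a significant false difference in about 77% of trials with no heterogeneity, and in 49%, 24% and 15% at SD 1, 2 and 3. This stands: the bias is systematic, but a false declaration is not certain.

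*Dose-based outcomes already exist.* They do, and that makes the repair cheap. The text nevertheless attaches DOAC type to the primary binary model.

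*Any missed dose may matter clinically.* That can justify the outcome. It does not justify reading a dose-count effect as behaviour.

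A reader might go further and infer that the primary reminder contrast is biased, because drop-outs and excluded interruptions ("Physician-initiated temporary treatment interruptions will not be considered non-adherence") shorten some periods. A patient followed for 2 of 13 weeks would score non-optimal with probability 1 − 0.55^(2/13) = 8.8% rather than 45%. The article does not support that inference. The comparison is within patient, over two nominally equal periods whose order is randomised. How truncated periods are scored is a detail an article leaves to the full protocol or analysis plan. A rough bound is also small: with homogeneous risk and drop-out spread evenly over a period, the mean score is 1 − 0.45/0.598 = 24.7%, about 20 points low. If all of the assumed 12% drop-out fell in the same condition, the contrast would move by 0.12 × 20.3 = 2.4 points, against a planned effect of 20.

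**Conclusion.** The point holds for the ancillary DOAC-type analysis. At equal per-dose behaviour the outcome definition produces an apparent disadvantage for twice-daily drugs, with an odds ratio of about 2.5 under homogeneous risk and about 1.4 to 2.0 under the heterogeneity examined. This rests on a 50:50 regimen mix, the 45% overall rate, and independent doses given the patient. The direction does not depend on the amount of heterogeneity; the size does. The DOAC-type interaction is also hard to interpret on this scale, though less severely.

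The reminder contrast is largely protected, and nothing here calls for replacing the primary model or the regimen-specific timing windows. The change should be made, but the trial's main conclusion does not hang on it.

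**What to change.** - Base the DOAC-type comparison and its Reminder Card interaction on taking adherence and timing adherence as proportions of doses. Alternatively, for this ancillary analysis only, use a per-dose binomial mixed model, or a complementary log-log model with log(evaluable doses) as offset.
- State that the DOAC-type coefficient from the binary model will not be interpreted as a difference in adherence behaviour.
- Note that the timing proportion removes the dose-count effect but still reflects the two windows; the taking proportion is free of both.
- Keep the primary logistic model for the reminder contrast. An analysis accounting for evaluable doses can be added as a sensitivity analysis for truncated periods.

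**Cost.** Wording and slightly more programming. No new data are needed, since intake date and time are already recorded electronically. The DOAC-type result will be on a different scale from the primary odds ratio. The offset model also assumes a constant per-dose rate and independent deviations within patient and period, which clustered lapses would violate.

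### On its most natural reading, the before-after comparison sets a 6-month any-deviation outcome against 3-month ones, which favours counseling and the pillbox even if behaviour does not change

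*Protocol article*

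**What the plan says.** All places are in the protocol article.

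- **Study Outcomes.** The primary outcome, non-optimal timing adherence, is "defined as ≥ 1 dose omitted or taken outside of 25% of the prescribed dosing schedule". Non-optimal taking adherence, a secondary outcome, has the same form and counts omissions only. On the windows for the primary outcome the section says: "It will be calculated for the observational phase and for the two interventional-phase periods separately".
- **Intervention.** The first window is 6 months long: "After the 6-month observational phase, patients will receive pharmaceutical counseling".
- **Randomization.** Each interventional period is 3 months long: "Group 1 will receive intake reminders for the first 3 months and Group 2 for the last 3 months".
- **Statistical Analyses.** The primary model is a "mixed-effects logistic model with Reminder Card (yes/no) as fixed and patient as random effect". The secondary analyses compare adherence outcomes between the two interventional periods and between "ii) observational and interventional phase, as in the primary analysis".
- **Discussion.** The second of these comparisons has a stated purpose: "We expect that counseling and MCCAs will have an additional adherence-improving effect, which we will assess in before-after comparisons".

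**The concern.** An outcome that turns positive at the first deviating dose depends on how many doses are observed. A patient followed for 6 months has twice as many chances to deviate as the same patient followed for 3. If the 6-month observational value and the separate 3-month values enter one logistic model with no term for length, the observational phase looks worse even when nobody has changed. The article itself expects adherence to be broadly stable over the study, which is the situation in which the artefact stands alone.

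The bias has one direction, in favour of the interventional phase. The before-after comparison is also the article's stated route to the effect of counseling and the pillbox. A package with no effect could therefore be reported as effective on both binary adherence outcomes.

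**Working it through.** **1. The plan's own figure.** Inputs from Sample Size Estimates: 130 participants, 12% drop-out, 45% without reminders, 20% effect, power 0.9, two-sided alpha 0.05. Completers: 130 × 0.88 = 114.4, taken as 114. Read the 20% as absolute (45% to 25%) and the two sets of 114 records as uncorrelated:

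- SE under no difference = √(2 × 0.35 × 0.65 / 114) = 0.0632
- SE under the alternative = √((0.45 × 0.55 + 0.25 × 0.75) / 114) = 0.0618
- Power = Φ((0.20 − 1.96 × 0.0632) / 0.0618) = Φ(1.23) = 0.89

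This reproduces the stated 0.9, so 20 points is a fair yardstick for the artefact, and 114 is used below.

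**2. Null model.** Each patient has a constant deviation rate λ that never changes. For a window of T quarters, P(at least one deviation) = 1 − E[exp(−λT)], with T = 1 for 3 months and T = 2 for 6 months. Rates are equal across patients (SD 0) or log-normal with SD 1 to 4 on the log scale. The article gives no such SD, so the range is an assumption. The article also attaches no window to its 45%, so both readings are shown.

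**3. Equal patients, by hand.**

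- 45% at 3 months: the 6-month rate is 1 − 0.55² = 69.8%, a gap of 0.45 × 0.55 = 24.75 points.
- 45% at 6 months: the 3-month rate is 1 − √0.55 = 25.8%, a gap of 19.2 points.
- 90% at 3 months: the 6-month rate is 1 − 0.10² = 99%, a gap of 0.90 × 0.10 = 9 points.

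**4. With heterogeneity.** The spurious gain is the 6-month rate minus the 3-month rate.

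| Log-rate SD | 45% at 3 months: 6-month rate (gain) | 45% at 6 months: 3-month rate (gain) |
|---|---|---|
| 0 | 69.8% (24.7) | 25.8% (19.2) |
| 1 | 63.0% (18.0) | 29.0% (16.0) |
| 2 | 56.8% (11.8) | 33.8% (11.2) |
| 3 | 53.5% (8.5) | 36.8% (8.2) |
| 4 | 51.6% (6.6) | 38.5% (6.5) |

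With a 3-month rate of 90%, the gain falls from 9.0 points (SD 0) to 4.4 (SD 2) and 2.6 (SD 4).

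**5. False significance.** A random-intercept logistic model was fitted to one 6-month and one 3-month record for each of 114 patients, with no true change and a likelihood-ratio test at 5% (500 simulated trials per case).

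| Log-rate SD | 45% at 3 months | 45% at 6 months | 90% at 3 months |
|---|---|---|---|
| 0 | 97% | 87% | 93% |
| 1 | 90% | 80% | 67% |
| 2 | 72% | 71% | 45% |
| 3 | 60% | 58% | 38% |
| 4 | 48% | 45% | 28% |

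Virtually all significant results favoured the interventional phase.

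**6. Equal windows.** With 3 months against 3, or 6 against 6, the expected difference under the same null model is zero.

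**The case against.** **The wording allows another reading.** Statistical Analyses speaks of periods in the first secondary comparison and of phases in the second, and both phases last 6 months. If the interventional value is any deviation over the whole phase, the windows are equal and the bias disappears. The reference to the primary analysis could mean only the type of model. This partly stands: the text does not exclude it. It fits less well with Study Outcomes, which has the outcome calculated separately for the two interventional periods, and with reuse of a model built on those per-period records. A reader might infer that the plan is irrevocably committed to unequal windows; the documents do not go that far.

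**A condensed article may leave derivations to the full protocol or SAP.** In general, yes. Here, however, the article names the windows and the model, and together they produce the mismatch. The objection has more force for non-optimal taking adherence, because the sentence on windows refers to the primary outcome and its extension to the taking outcome is presumed.

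**The size is uncertain.** This stands. Under equal patients the gap is p(1 − p), so a 3-month rate of 45% lies close to the maximum of 25 points at p = 50%. A higher rate under electronic monitoring, or stronger heterogeneity, shrinks it. A reader might infer that the artefact is always as large as the 20-point planned effect; that needs little heterogeneity and a mid-range rate.

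**The comparison is secondary and not randomized.** This stands and limits the severity. Timing and taking adherence as proportions enter the same comparison without this dependence on window length, and could expose a spurious binary result. A reader might infer that the primary result, or the whole before-after evaluation, is compromised. Neither follows: reminders are compared over 3 months against 3, and the proportions remain usable.

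**Conclusion.** The point holds for the two binary outcomes in the comparison of the observational with the interventional phase, on the most natural reading of the article. On that reading the direction of the bias is certain and favours counseling and the pillbox.

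Its size is conditional. It is about 7 to 25 points if 45% is the 3-month rate, about 6 to 19 points if it is the 6-month rate, and under 10 points if the 3-month rate is near 90%. These ranges assume constant rates within patients and a log-rate SD between 0 and 4. The bias approaches zero only if nearly every patient is either always or never non-optimal. In every case examined, a nominal 5% test was falsely significant far more often than 5%.

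This should be fixed before analysis. It is not a flaw in the randomized evidence on reminders.

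**What to change.** State in the analysis section or the SAP that, for the comparison of the observational with the interventional phase, both outcomes based on at least one deviating dose are computed over windows of equal length. Either choice works:

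- **3 months against 3 months.** Use the last 3 observational months against each 3-month interventional period in the same mixed model. Cost: the first 3 observational months go unused for these two outcomes.
- **6 months against 6 months.** Use any deviation over the whole of each phase. No data are discarded, but the single interventional value mixes months with and without reminders.

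The proportion outcomes can keep the full 6 observational months. The change is one sentence and needs no new data.
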